Even less is known about potential moderators of the effectiveness of FG-cs: in which families, under what circumstances will family group conferences have the best results? Effectiveness studies try to find overall effects, whereas not all families are likely to benefit from one approach [17]. As Farrell, Meyer, Kung, and Sullivan (2001, p. 216) stated, “one cannot assume that an intervention program is equally effective with all participants” [18]. Therefore, analysis of overall program effects might suggest that programs did not work when in fact they did work for some subgroups [19]. Identifying moderators of the intervention effectiveness can be useful for identifying and engaging those who are most likely to benefit [20], and provides opportunities to adjust the programs to improve effectiveness for certain subgroups of clients.

In addition to potential moderating effects of family characteristics, program integrity may also moderate the effectiveness of FG-cs. An FG-c starts off with an initializing stage, than the actual conference takes place, and subsequently, the Family Group plan needs to be carried out. It is important to determine whether all stages belonging to a FG-c are carried out and to what extent the Family Group plan has been carried out as intended. This information can be used to determine which stages of the FG-c are critical for the achievement of potential positive results.

To increase the knowledge about the effectiveness of Family Group Conferences in youth care, we will perform a randomized controlled trial (RCT). In contrast to previous research that had several methodological shortcomings, this study will provide the opportunity to draw (scientifically robust) conclusions about the effectiveness of FG-c’s. In addition, it will become clear which characteristics of the approach, of the participating families and which characteristics of the family managers who should support the implementation of the Family Group plans are important to reach the best results. Finally, in times in which large amounts of public money are spent on ‘family autonomy and participation in child care’, operationalized in Family Group Conferences, it is important to base policy decisions concerning whether or not to continue those investments on clear numbers regarding the costs and benefits of Family Group Conferences. Therefore, the present effectiveness study will be accompanied by a cost-effectiveness analysis.

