## Methods and design

The study aims to answer two main questions. The first question is whether Family Group conferences in youth care are effective as a decision making model in terms of increased child safety, involvement of the social network, perceived control over problems and a reduction in use of professional care. In order to determine the effectiveness of FG-cs, a RCT will be carried out including 300 families referred to Youth Care Agency Amsterdam (YCAA). Moreover, costs associated with FG-c will be identified in order to determine the cost-effectiveness of FG-cs.

The second research question concerns the moderators of the effectiveness of FG-c. Both participant and program characteristics will be examined as potential moderators. Program characteristics to be examined are program integrity and characteristics of FG coordinators and family managers (responsible for supporting the implementation of the FG plans developed by the broader social network of the family). It is crucial to examine program integrity (i.e., the extent to which different phases of a FG-c have been conducted according to the protocol). Without having established program integrity, there is the risk of concluding that FG-cs are not effective, whereas in fact the FG-c has not been fully implemented. Furthermore, it is possible that a successful FG-c has taken place, but the plan developed in the FG-c has never been carried out. It is therefore important to determine whether all stages of the FG-c have been implemented as planned.

Additionally, it is important to examine family characteristics as potential moderators of the effectiveness of FG-c. It is plausible that FG-cs are not equally effective for every participating family. For example, families with a small social network, or with limited possibilities to attend a conference or with other particular characteristics that hamper the organization or carrying out of a FG-c or the FG plans are less likely to attend a FG-c. Identifying those families who are less likely to fulfill an FG-c may result in savings.

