### Design

A randomized Controlled trial will be conducted to examine whether FG-cs are effective in changing: (1) child’s safety (i.e., decrease in (risk for) abuse/neglect; less supervision orders or shorter supervision order; less or shorter out of home placement); (2) the involvement of the broader social network; (3) perceived control over the problems in the families, empowerment of parents; improvement of family functioning; (4) less use of professional care. A second aim is to study whether the effectiveness of FG-c is influenced by characteristics of the implementation of the methodology, characteristics of the family managers (such as education, or attitude towards FG-c), or by family characteristics (such as size of the social network, ethnicity or family type: single/married).

Using computerized randomization two comparable groups will be formed. Until the inclusion of 300 families is completed (presumably within 6 months), every family starting care at Youth Care Agency Amsterdam (YCAA) will be randomly allocated to care with or without a Family Group conference. Because allocation to care with a FG-c will not always result in an actual Family Group conference and/or an approved Family Group plan, 200 families will be assigned to care with FG-c and 100 families to care without FG-c. Five multi-informant/source (parent, family manager; FG-coordinator; member of the family’s social network; child (if > 8 years of age), and file analysis) assessments will be carried out in both groups. Pre-tests will take place before FG-cs starts. Subsequently, in both groups post-tests will be carried out 1, 3, 6 and 12 months after the FG-c has taken place (see also Figure 1 for the flow chart).

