### Study sample

We aim to include *N* = 300 families, who will be randomized in a 2 (FG-c): 1 (control group) ratio to ensure that there is enough power to also conduct the planned moderator analyses. These groups are large enough to detect effects of FG-c’s.

Given the goal of YCAA to carry out 800 FG-c’s each year, the inclusion of 300 families will be completed within six months. This sample size is sufficient to test the hypotheses with an alpha of .05 and a small to medium effect (*d* = .35). FG-c can be used for all families, so there are no exclusion criteria in this study.

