### Statistical analyses

Missing data will be imputed so that all participants will be included in the analyses, and using LISREL 8.8, the multiple imputation will be carried out by the expectation maximization algorithm [37]. Both an intention to treat as well as a completer analysis will be performed.

In order to examine the effectiveness of FG-c overall effectiveness will be examined for all outcome measures by conducting an ANCOVA, with the outcome measures at post-test as dependent variables, treatment condition as factor and pre-intervention scores of the outcome variables as co-variates, as is recommended for RCTs using pre- and post-tests [38]. Effect sizes will be computed as Cohen’s d, based on adjusted means and standard errors.

For categorical moderator analyses, the same ANCOVA’s will be conducted, with the moderators as factor. Post-hoc analyses for moderator effects will be conducted by splitting the file according to the moderator and again conducting an ANCOVA and calculating effect sizes separately for each group. Regression analyses will be conducted for the continuous moderators.

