Additionally, a rich set of instruments will be used, so that if there is any effect on any of the outcomes, there is a large likelihood to identify this effect. Moreover, potential moderators in terms of program as well as participant characteristics will be examined, so that the present study will provide information on when and for whom FG-cs are most likely to be effective. Program integrity will be examined and fulfillment of each phase of FG-c will be registered. Finally, the cost-effectiveness of FG-c will be examined: valuable information for both politicians as well as families who invest time in a FG-c.

However, there are also several limitations, which may threaten the value of our study. First, there is a risk in having this many informants and assessment moments (5 time points). There is the risk that the families or other informants will drop out of the study. We will put a lot of effort in maintaining the families in the study. Thankfully, the research group has experience with motivating for and retaining participants in research [39], but this always needs full attention.

Additionally, TAU in the control group may cause smaller effect sizes when compared to no treatment in the control group. However, as the research question is whether FG-c adds something to the usual child care services, this is the most logical design.

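### Moderators are tested on every outcome and followed by split-file ANCOVAs, with no interaction criterion and no stated gate, although the Background promises clear answers on which characteristics matter

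*Protocol article*

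**What the plan says.** The Methods and design section makes moderators the second of two main research questions. Design gives open lists of examples: education and attitude for the family manager; network size, ethnicity and family type for the family. The Moderators section adds a risk list and a child problem checklist, which makes seven. It also lists several features that exist only where a conference is held.

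Under Statistical analyses, the overall ANCOVA is run on every outcome measure. Categorical moderators get the same ANCOVAs with the moderator as a factor, and continuous ones get regression. Then: "Post-hoc analyses for moderator effects will be conducted by splitting the file according to the moderator and again conducting an ANCOVA", with effect sizes calculated in each group.

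The only significance level in the article stands in Study sample: "This sample size is sufficient to test the hypotheses with an alpha of .05" and "a small to medium effect (*d* = .35"). The sizes are "We aim to include *N* = 300 families" and "200 families will be assigned to care with FG-c and 100 families to care without FG-c".

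On what will be concluded, the Background says "it will become clear which characteristics of the approach, of the participating families" and of the family managers are important for the best results. The Discussion is milder: "the present study will provide information on when and for whom FG-cs are most likely to be effective". Neither place calls the moderator results exploratory.

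**The concern.** Two features of the written analysis can produce an apparent moderator where none exists.

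The first is the number of tests. Each moderator is crossed with every outcome, and the article fixes neither a ranking of moderators nor one outcome on which moderation is to be judged.

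The second is the criterion. Entering a moderator as a factor can mean testing its interaction with treatment, or only adding its main effect; the text does not say which. The next step it describes is an ANCOVA within each subgroup. Significance in one subgroup and not in the other says little about whether the effect differs between them.

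The results are meant to show for whom family group conferencing works, and the article is addressed to policy makers. A chance subgroup finding presented as a clear answer could influence which families are offered a conference.

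**Working it through.** **Inputs.** N = 300, 200:100, d = .35 and alpha .05, all from Design and Study sample. Four safety instruments (LIRIK, safety line, CAPI, Succint) come from Table 1. Assumptions: two-sided tests, the correlations below, d taken on the scale of the analysis, and each moderator tested by one valid interaction test.

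**Reproducing the plan's figure.** The article gives no power; I assume 80%. With 2:1 allocation, controls needed = (1 + 1/2) × [(1.960 + 0.842)/0.35]² ≈ 96.1, so 97 controls and 291 in total, close to 300. At 200:100 the power for the main effect is about 81.5%. The sample size therefore fits a main effect of .35.

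**Number of moderators.** Seven are named that could be defined in both arms. Two are less certain. Table 1 has no row for network size, only the number of network members at the conference. The Moderators section records the manager's support for the conference as part of the manager's role, which Table 1 schedules after the pretest. Without these two, five remain. The lists in Design are open, so seven is not a ceiling.

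**Chance of at least one false moderator, none being real.** For m independent tests it is 1 − 0.95^m. Correlated cases are simulated as equicorrelated normal test statistics with a cut-off of 1.96.

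| Moderators | One outcome, one post-test | Four safety instruments, one post-test |
|---|---|---|
| 7, independent | 1 − 0.95^7 = 30% | 1 − 0.95^28 = 76% |
| 7, correlated | 23% (correlation 0.5); 15% (0.8) | 57% (0.5 among moderators, 0.5 among outcomes); 45% (0.5 and 0.8) |
| 5, independent | 1 − 0.95^5 = 23% | 1 − 0.95^20 = 64% |
| 5, correlated | 13% (0.8) | 37% (0.5 and 0.8) |

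The ranges are therefore about 13-30% and 37-76%. Correlations stronger than those assumed would lower them. Secondary outcomes, or repetition over the four post-tests, would raise them.

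**Split files read as separate tests.** Take a moderator that halves the sample (100:50 in each half) and a true effect of .35 in both halves.

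- The noncentral t gives 52% power in each half (51.9%).
- P(exactly one half significant) = 2 × 0.519 × 0.481 = 0.499.
- For a 30/70 split (60:30 and 140:70) the powers are 34.0% and 66.3%. The chance is 0.340 × 0.337 + 0.660 × 0.663 = 0.55.

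So with an identical effect in every family, a one-sided pattern appears about half the time.

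**The case against.** The strongest reply is that this is a condensed article. Multiplicity adjustment, a ranking of moderators and an exploratory label are commonly left to an analysis plan, and none is shown. A reader might infer that the trial tests everything at an unadjusted .05. The article does not say so: .05 stands in the sample-size sentence, and nothing is said about adjustment either way. This part of the reply stands, and the error rates above are conditional on that assumption.

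Second, the split-file step is called post-hoc, comes after the moderator ANCOVA and includes effect sizes. It may be meant only to describe a moderator effect already found, in which case it adds no false moderators. That reading is reasonable. But the section states no such gate and names no interaction test that could serve as one.

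Third, the claims vary in strength. The Discussion promises only information and calls the moderators potential. Only the Background sentence is strong.

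Fourth, a reader might take "Identifying those families who are less likely to fulfill an FG-c may result in savings" as a plan to save money on the basis of subgroup effects. In context it concerns families unlikely to attend or complete a conference, so it is not evidence for this point.

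What no unseen document would mend is the published wording itself: subgroup ANCOVAs without an interaction criterion, next to a promise of clear answers.

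**Conclusion.** The point holds as a defect in what the article fixes and promises; it is cheap to repair. The moderator analysis spans every outcome, lacks a stated interaction criterion and ends in ungated split-file ANCOVAs, and the Background sentence is stronger than that analysis can bear.

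The size rests on there being no true moderator, testing at .05, a count of five to seven and the assumed correlations. It would be tempting to conclude that a false moderator is likely. That is not supported throughout: on one outcome the chance stays at or below 30%, and on four instruments it falls below one half in the more strongly correlated cases. The 50% figure for split files applies only if they are run without a gate and read as separate significance tests.

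**What to change.** In Statistical analyses, state that:

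- moderation is judged only by the treatment-by-moderator interaction;
- split-file results are given as effect estimates with confidence intervals, to describe an interaction already found, and not as separate tests;
- moderator results are exploratory, except for a short pre-named list tested on one pre-named safety outcome with multiplicity adjustment, if such a list is wanted. That outcome would have to be chosen, since the article lists several safety indicators and no leading one.

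Reword the Background sentence to say that moderator findings generate hypotheses, and bring the Discussion into line.

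This takes a few sentences and no new data. The price is a weaker claim about who benefits, and adjustment would reduce power that is already low. For an interaction of .35 with an even split, the standard error is √[2 × (1/50 + 1/100)] = 0.245, so power at .05 is Φ(0.35/0.245 − 1.960) ≈ 30%. That is a reason to keep any adjusted list short.

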### Moderators

*Characteristics of the Family Group-conferences (FG-c)*, such as number of families per FG-coordinator, location, time to start of FG-c, number of members of the network present at the FG-c, will be registered on the registration form developed for this specific study.

Additionally, specific characteristics of the Family Group-conference, related to the *implementation of the FG-c*, will be registered on this form too, such as whether the separate phases of the FG-c have been followed as intended, duration of these phases, and whether the plan is carried out as intended and who was responsible for the carrying out of the plan, and whether this person took the assigned role.

Moreover, the *role of the family manager* in the carrying out of the FG-c will be monitored with the registration form: did the family manager bring the FG-c up within the intended period of time (2-6 weeks after start)? Was the family manager supportive of FG-c (and why (not))? Did the Family manager leave control with the family (and why (not))?

*Characteristics of the families* that may affect the effectiveness will be assessed. Demographics will be coded from the file research and information that is not present in the YCAA file will be asked with a questionnaire. Risk factors will be assessed with a risk list that consists of a combination of the Washington Prescreen Risk Assessment instrument [35], for the penal law cases and the Delta risk list specifically developed for civil law cases.

*Problems of the child* will be assessed with the Brief Problem Checklist [36], to be filled out by the parents (if the child is younger than 8 years of age) or the child (if the child is older than 8). This is a validated short questionnaire that assesses problems of the child.

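### Implementation variables that arise after randomisation and have no control-arm counterpart are analysed as moderators of the FG-c effect, which the stated models cannot estimate

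*Protocol article*

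**What the plan says.** The Abstract, Methods and design, and Design sections all make implementation a moderator of effectiveness, beside family and family manager characteristics. Methods and design puts program integrity inside the second main research question.

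The Moderators section lists the items. They include time to the conference, "number of members of the network present at the FG-c", adherence to the separate phases, "whether the plan is carried out as intended and who was responsible for the carrying out of the plan", and how the family manager acted (raised the conference in time, supported it, left control with the family).

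The Design section, just after Figure 1, says that four items are assessed for families in the FG-c condition: concept explained, conference held, plan formulated, plan carried out. Execution of the plan is recorded at the 1-, 3- and 6-month post-tests.

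Statistical analyses gives one recipe. For categorical moderators the same ANCOVAs "will be conducted, with the moderators as factor", and then: "Post-hoc analyses for moderator effects will be conducted by splitting the file according to the moderator", with a further ANCOVA and effect size in each group. Continuous moderators go to regression. Baseline characteristics and FG-c-only variables are not distinguished.

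The moderator question also shapes the design. Study sample ties the unequal allocation of the 300 families to power for these tests: "who will be randomized in a 2 (FG-c): 1 (control group) ratio to ensure that there is enough power to also conduct the planned moderator".

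**The concern.** Moderation means that the FG-c-versus-control effect differs across levels of a variable. That needs a variable with values in both arms, and one that the allocation did not produce. The implementation items fail on both counts.

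Any result the recipe gives for them compares families who implemented with families who did not, within one arm. The protocol itself expects these to be different families. Methods and design says that families with small networks, or with little opportunity to attend, are less likely to take part in a conference. The Design section gives the expected shortfall in conferences and approved plans as a reason for unequal allocation.

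At stake is part of the second research question. Background says the integrity data can show which stages are decisive for good results, which is a causal reading. A within-arm association reported as moderation in an RCT would carry an authority it does not have.

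**Working it through.** **1. The plan's own sample size.** Inputs from Study sample and Design: alpha .05, d = .35, and "200 families will be assigned to care with FG-c and 100 families to care without FG-c". Power and sidedness are not stated; I assume 80%, two-sided.

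- Controls needed = (1.960 + 0.842)² × (1 + 1/2) / 0.35² ≈ 96.1, so 97. FG-c: 2 × 97 = 194. Total 291, close to the planned 300.
- Power at 200:100: SE = √(1/100 + 1/200) = 0.1225; 0.35/0.1225 − 1.96 = 0.898; power 81.5%.

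So "This sample size is sufficient to test the hypotheses with an alpha of .05 and a small to medium effect" (d = .35) is reproduced for the main effect. The concern does not touch it.

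**2. Can the interaction be estimated?** Let C = 1 for FG-c and 0 for control, and let M = 1 if the plan was carried out.

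- *Controls coded 'no'.* M = 1 only where C = 1, so C × M = M in every row. The design matrix [1, C, M, C×M] has rank 3 of 4, and the interaction cannot be estimated.
- *Controls left missing.* Only FG-c rows remain. C is constant, C × M again equals M, and neither the condition effect nor the interaction exists.
- *Splitting the file, with half of the FG-c arm implementing (assumption).* The 'yes' stratum has 100 FG-c families and 0 controls, so the condition ANCOVA and its Cohen's d cannot be computed. If controls are coded 'no', all 100 fall in the other stratum, beside the 100 FG-c families who did not implement.

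Time to conference and number of network members go to regression rather than file-splitting. They have no control value either, so the same result holds. This step does not depend on the 50% figure.

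**3. What the remaining contrast would show.** Simulation, 1,500 trials per scenario, 200:100, with the true effects of FG-c and of implementation both zero. Assumptions: an unmeasured prognosis U; pre-test correlating 0.5 with U and entered as covariate; about 50% implemented; correlation of U with outcome 0.3 or 0.5; odds ratio (OR) of implementation per SD of U from 1 to 3. Entries are the adjusted difference, implemented minus not implemented, and the rate of p < .05.

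| OR per SD of U | corr(U, outcome) 0.3 | corr(U, outcome) 0.5 |
|---|---|---|
| 1 | 0.00 SD, 5% | 0.00 SD, 5% |
| 1.5 | 0.09 SD, 9% | 0.15 SD, 20% |
| 2 | 0.14 SD, 18% | 0.23 SD, 39% |
| 3 | 0.21 SD, 31% | 0.35 SD, 72% |

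Comparing each FG-c subgroup with all controls does not help. At correlation 0.5 and OR 3, the implementers appear to gain 0.17 SD and the non-implementers to lose 0.17 SD, with no true effect.

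These settings imply a pre-test-outcome correlation of only 0.5 × 0.3 = 0.15 to 0.5 × 0.5 = 0.25. A pre-test that captured more of the prognosis would leave less bias.

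**4. A legitimate moderator, for comparison.** For a T1 variable in both arms, split 50/50, outcome SD 1: SE of the interaction = √(1/50 + 1/100 + 1/50 + 1/100) = 0.245. Power for an interaction of 0.35 SD: 0.35/0.245 − 1.96 = −0.53, about 30%. Detectable with 80% power: 2.80 × 0.245 ≈ 0.69 SD.

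**The case against.** The best defence is that the article never says a condition-by-moderator term will be fitted to FG-c-only items. For those, the ANCOVA could be read as a within-arm analysis adjusted for the pre-test, which is close to the remedy below. Methods and design also gives a descriptive reason for recording integrity: not to call FG-c ineffective when it was never delivered. Both points are fair. But the within-arm reading still presents a non-randomised contrast as moderation of effectiveness, and the text does not mark these items off from true moderators.

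The word post-hoc may already mean that splitting only follows a detected effect. That is plausible for baseline moderators, but it does not supply controls to a stratum that has none.

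Some stronger readings are tempting but not supported:

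- *That the bias is certain, or at least as large as d = .35.* It requires implementation to depend on prognosis beyond the pre-test covariate. A gap in prognosis is not a gap in outcome, and after the stated adjustment only the most extreme scenario reaches 0.35 SD.
- *That child problems are a post-randomisation moderator.* Table 1 marks that checklist at T1 as well as T4 and T5, and nothing says the later scores will serve as moderators.
- *That tests of family manager characteristics are invalid because families share managers.* The document gives neither the number of managers nor the variation between them, and this modelling detail is commonly left to an SAP.
- *That all moderator analyses fail.* Family characteristics and family manager characteristics recorded at T1 are valid moderators.

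**Conclusion.** The concern holds for the implementation variables. That their moderation cannot be estimated follows from the stated design and needs no numerical assumption. The article says outright that the conference and plan items belong to the FG-c arm. For time to conference and network members present it follows from what they measure, and the family manager's role items are mostly specific to FG-c.

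The size of the possible error is conditional: about 0.09 to 0.35 SD, with false-positive rates of 9% to 72% under the assumptions of step 3, and no bias if implementation is unrelated to residual prognosis. The document makes some dependence plausible but gives no figure for it.

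The sample size and the randomised comparison of the arms stand. The part of the second research question that concerns implementation cannot be answered as moderation.

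**What to change.** - Limit moderator tests to variables measured at T1 in both arms: demographics, the risk list, T1 child problems and family manager characteristics. Test each by a condition-by-moderator term in the ANCOVA or regression, and split the file only to follow up an interaction.
- Move phases followed, plan carried out, time to conference, network members present and the family manager's role in the conference to a separate analysis. Report them as explicitly non-causal associations within the FG-c arm, adjusted for T1 scores and baseline family characteristics.

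The cost is wording and one model term; data collection, sample size and the main comparison do not change. The price is that conclusions about which stages matter become descriptive. The interaction tests that remain will also detect only large differences, about 0.69 SD with 80% power for an evenly split moderator, which should be said where the article claims power for moderator analyses.
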